### Follow-up

The follow-up period is 12 months. In order to strengthen the monitoring adherence, most patients will be contacted through WeChat, QQ chat, mobile phones, emails and the regular outpatient interview. Follow-up will be scheduled on the third day and the first, third, sixth and 12th months postoperatively.

### Data management and statistical analysis

One of the researchers, who is an expert in statistics and blind to treatment assignments, will perform the analysis. The sign that a PA has survived will be set as the higher PTH ratio between the grafted and non-grafted forearm, which will be analyzed by a *Χ*^2^ test. All parameters will be analyzed by appropriate statistics with SPSS 22.0, including categorical data and normally distributed numerical data. The former will be compared using a *Χ*^2^ test or Fisher’s exact test and the latter will be analyzed by a *t* test and the Mann-Whitney *U* test if skewed. A Cox model will be used to verify the factors affecting PA survival. Data will be collected in the CRF and consent forms are preserved in a locked computer kept in a locked room. Each participant will be identified by randomization number to ensure the confidentiality of this study.

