**Methods:**

In total, 280 patients will be enrolled in this study and randomly divided into two groups: 140 patients with transplanted parathyroid glands in the traditional sites (group A) and the other 140 transplanted in the novel sites (group B), close to the antecubital veins. The serum concentration of PTH and calcium ion from both forearms will be measured and monitored regularly for 12 months. The primary outcome of this trial will be the survival of grafted glands, defined as the ratio of PTH between the grafted vs. the non-grafted forearms being no less than 1.5. The secondary outcome is hypoparathyroidism, defined as the PTH level from the non-grafted forearms being less than 15 pg/ml (normal range 15–65 pg/ml).

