### PA protocol

Patients will undergo operations in the supine position under general anesthesia. The removed parathyroid glands will be placed in sterile physiological salt solution at 4 °C until confirmed by the frozen-section diagnoses. The parathyroid glands will be sliced into 2–4-mm cubes and mixed with 0.5 cc sterile physiological salt solution in a 1-cc syringe. The parathyroid fragments will be subcutaneously injected into the non-dominant forearm with a 16-G needle [19].

The novel site method means choosing the graft site close to the antecubital veins, including the cephalic vein, the median cubital vein and the basilic vein. During the follow-up, blood samples will be taken from the vein near the graft site (Fig. 3), as well as from the opposite forearm. The traditional site method means general transplantation further away from the relevant antecubital veins. In Fig. 3, the novel sites are points A and B and the traditional are points C and D. All of the grafted forearms from the two groups will be pressed gently immediately after transplantation. The blood samples will be taken at five different time points: 3 days, 1 month, 3 months, 6 months and 12 months after transplantation.

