#### Preoperative variables

These will be age, sex, clinical history, diagnosis, treatment, feeling of dump or twitch, limb weakness, serum PTH concentration, and thyroid-stimulating hormone (TSH), triiodothyronine (T3), thyroxine (T4), calcium and phosphate levels. Concomitant medication will also be recorded for oral supplementation with calcium and calcitriol soft capsules.

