### Subgroup analysis

We will compare the primary outcome between subgroups characterised by: (1) high vs. low adherence; (2) malignant vs. non-malignant thyroid disease; (3) age categories (18–45, 46+ years); (4) gender and Body Mass Index (BMI) categories (< 25, 25+ kg/m^2^); and (5) parathyroid numbers autotransplanted and preserved.

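### The Cox model for graft survival does not fit an outcome defined, sized and tested as yes/no; separately, the adherence subgroup is defined after randomisation

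*Protocol article*

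**What the plan says.** The Abstract (Methods) gives the primary outcome as "survival of grafted glands, defined as the ratio of PTH between the grafted vs. the non-grafted forearms being no less than 1.5". Study design repeats the threshold and compares the percentages reaching it in the two arms. Sample size calculations uses 45% and 65%, two-sided alpha 0.05 and power 0.90, giving 128 per arm and 280 in all after allowance for loss.

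Data management and statistical analysis says "The sign that a PA has survived will be set as the higher PTH ratio between the grafted and non-grafted forearm, which will be analyzed"; the test it names is chi-squared. A few sentences later it adds: "A Cox model will be used to verify the factors affecting PA survival".

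On timing, PA protocol states: "The blood samples will be taken at five different time points: 3 days, 1 month, 3 months, 6 months and 12 months after transplantation". Follow-up states: "The follow-up period is 12 months".

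Subgroup analysis begins: "We will compare the primary outcome between subgroups characterised by: (1) high vs. low adherence". It then lists malignancy, age, gender and BMI, and numbers of glands transplanted and preserved. Adherence is not defined there. The only other use of the word, under Follow-up, concerns patients keeping to monitoring after surgery. Limitations says that factors bearing on graft survival belong to a later investigation.

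**The concern.** A Cox model needs a time to a defined event. The outcome here is a status re-read at each visit, and no section says that a ratio which has crossed 1.5 stays on that side. The analyst would have to create an event, and each choice changes the question:

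- If the event is loss of function, grafts that have not yet reached 1.5 have nothing to lose.
- If the event is first reaching 1.5, one high reading at any visit counts as success, whatever the later readings show.

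Neither is the proportion that the chi-squared test compares. Factor effects could then disagree with the primary result because of the definition alone.

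The adherence subgroup is a separate problem in a separate analysis. Keeping to follow-up arises after allocation and could differ between arms. It also decides whether the ratio is observed at all. Patients with the same adherence level in the two arms need not be comparable.

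**Working it through.** **1. The plan's own figure.** With p1 = 0.45, p2 = 0.65, mean 0.55, z = 1.960 and 1.2816:

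n = [1.960·√(2·0.55·0.45) + 1.2816·√(0.45·0.55 + 0.65·0.35)]² / 0.20² = (1.379 + 0.883)² / 0.04 ≈ 127.9, so **128 per arm**.

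This matches the protocol, and power at 128 is 0.900. Raising 128 to 140 allows 1 − 128/140 = 8.6% loss. Graft survival was therefore planned as a binary proportion.

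**2. Ties.** There are five visits, so at most five distinct event times for up to 280 patients. Assume the planning rates hold at every visit; the article does not tie them to one. First success at day 3 would then occur in 0.45·140 + 0.65·140 = 63 + 91 = 154 of 280 patients, all tied at the first visit.

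**3. A different question.** If visits were independent, the share ever reaching 1.5 would be 1 − 0.55⁵ = 95% (traditional) and 1 − 0.35⁵ = 99.5% (novel), against 45% and 65% at any one visit. Independence is extreme, so a range of latent within-patient correlations was simulated. Shares come from 200,000 patients per arm. Hazard ratios (novel against traditional) are averages over 200 trials of 140 per arm. The correlations are assumptions, not figures from the protocol.

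| Correlation | Ever ≥1.5, trad. / novel | Falls from ≥1.5 to <1.5 at least once, trad. / novel | HR, first ≥1.5: Breslow / Efron | HR, first <1.5: Breslow / Efron |
|---|---|---|---|---|
| 0 | 94.9% / 99.5% | 80.6% / 75.6% | 1.44 / 1.70 | 0.64 / 0.55 |
| 0.3 | 86.2% / 96.2% | 67.0% / 62.7% | 1.43 / 1.64 | 0.64 / 0.57 |
| 0.5 | 79.3% / 92.4% | 56.2% / 52.6% | 1.44 / 1.64 | 0.65 / 0.59 |
| 0.7 | 71.1% / 86.9% | 43.2% / 40.4% | 1.43 / 1.63 | 0.64 / 0.58 |
| 0.9 | 59.9% / 78.1% | 24.8% / 23.2% | 1.46 / 1.67 | 0.64 / 0.57 |

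Even at correlation 0.9, the share ever reaching 1.5 exceeds the per-visit rate by 13 to 15 points. On the same data, the tie method alone moves the first-success hazard ratio from about 1.44 to about 1.65.

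**4. Capacity of a binary model.** The planning rates imply an odds ratio of (0.65/0.35)/(0.45/0.55) = 2.27. With 128 per arm, the rarer outcome (ratio below 1.5) numbers 0.55·128 + 0.35·128 = 70.4 + 44.8 ≈ 115. Seven single terms (arm, malignancy, age, sex, BMI, glands transplanted, glands preserved) would have 115/7 ≈ 16 each.

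**5. Adherence.** No arithmetic applies. Subgroup analysis uses adherence to divide the primary outcome, and Follow-up uses the term for monitoring after surgery. The other listed subgroups are fixed before or during surgery; this one is not.

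**The case against.** The best defence is that a Cox or discrete-time model can be sound for a defined first event, that ties have standard handling, and that an article may leave event, origin and censoring to a fuller document. That much stands. A reader might infer that the factor results would be invalid, and the text does not support that. What remains is a mismatch in the stated text: the model is applied to the same survival that the article defines, sizes and tests as a proportion. A fuller plan could make it coherent only by adding an event that the article does not contain.

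Other stronger readings also fail:

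- **Reversibility.** A reader might take it as stated. It is an inference from a threshold on repeated readings, and its frequency is unknown.
- **Misreading rates.** One might assume that 10% of readings on a working graft fall below 1.5 and get 1 − 0.9⁵ = 41% misjudged over five visits. No such rate is given. Rates of 5% to 20% give 23% to 67%, and errors are assumed independent.
- **Adherence in the Cox model.** Nothing says it enters; these are two analyses.
- **BMI.** The preoperative list ("These will be age, sex, clinical history, diagnosis, treatment, feeling of dump or twitch, limb weakness, serum PTH concentration" and further items) does not name it. A condensed list does not show that the case report form lacks it.
- **Subgroup wording.** Comparing the outcome between subgroups may be loose shorthand. The absence of a named interaction test is not an error.
- **Purpose.** The Abstract and Background present the study of factors mainly as later work, so it should not be read as a main aim.

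**Conclusion.** The point holds in limited form. The Cox model is mismatched to a yes/no outcome read at five visits, and its hazard ratios, as stated, would not address the quantity that the primary test addresses. That conclusion rests on the article's own definition, sample size and test. The size of the discrepancy rests on assumed correlations and on constant rates of 45% and 65% at each visit. Independently, arm comparisons within adherence strata are not randomised comparisons. This takes adherence in its only other documented sense, keeping to follow-up.

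The chi-squared comparison and the sample size stand. Only secondary factor and subgroup analyses are affected, but the change is cheap and should be made.

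**What to change.** - **Factor model.** Replace the Cox sentence with logistic regression of ratio ≥1.5 at one named visit, for example 12 months as the end of follow-up, on arm and on baseline or intraoperative factors. Add a GEE or mixed logistic model over the five visits as support.
- **Subgroups.** Assess the remaining subgroups by arm-by-subgroup interaction in the logistic model.
- **Adherence.** Drop this subgroup, or label it non-randomised and exploratory.
- **Consistency.** Reconcile Data management and statistical analysis with Limitations on whether factors are studied in this trial or later.

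Cost: the time-to-event summary is lost. Interaction tests will be imprecise: with two equal subgroups, each arm effect has twice the overall variance V, so their difference has 2V + 2V = 4V and twice the standard error. The changes are to wording, and N stays at 128 per arm before loss. Trial status gives completion in December 2018, and the article is dated January 2019. The change should therefore be recorded and dated before the analyst, who is to stay blinded until the final analysis is complete, learns the allocation.

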### Subgroup analysis

We will compare the primary outcome between subgroups characterised by: (1) high vs. low adherence; (2) malignant vs. non-malignant thyroid disease; (3) age categories (18–45, 46+ years); (4) gender and Body Mass Index (BMI) categories (< 25, 25+ kg/m^2^); and (5) parathyroid numbers autotransplanted and preserved.

### Dissemination policy

Trial results will be disseminated to participants through emails, outpatient interviews or social media, including the condition of the transplanted parathyroid glands and the serum levels of PTH and calcium. In particular, those patients developing hypoparathyroidism will be assessed for the number of days needed to adjust their hypocalcemia to a normal level. At the end of the study, we will publish the results as references for health care professionals, the public, and other researchers.

### Data monitoring

An interim analysis will be performed when each group has 140 subjects with a completed 12-month follow-up. The interim analysis will re-evaluate the assumptions made for the study sample size calculation. If the percentages of the 1.5 ratio in the experimental group are obviously higher than those in the control group, the sample size will be re-estimated unless the trial has to be stopped as a result of the interim analysis.

We will perform an interim analysis of each 70 subjects, which focuses on differences of PA survival with different methods. The consents and clinical data will be monitored not only by the supervisor but also by the Data Monitoring Committee in Tongji Hospital, which is independent from this study and has no competing interests.

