**Fig. 1 Fig1:**
[figure not shown]
Standard Protocol Items: Recommendations for Interventional Trials (SPIRIT) Figure: the schedule of enrollment, interventions, and assessments

The allocation envelope will be opened by the surgeon when conducting the interference. It will not be possible to mask the treatment allocation from the treating surgeon. Nevertheless, measures will be taken to minimize bias:The patients will not be informed regarding whether they will receive the novel site or the traditional site methodTo minimize detection and selection bias, the exact method of PA will not be documented in the medical recordsThe investigator performing the statistical analyses will be blinded to treatment assignments until the final analysis is completed

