### Sample size calculations

The experimental group involves the participants with PA at the novel sites closer to the cephalic vein, while the participants in the control group generally receive subcutaneous transplantion. Since the survival rate of the traditional assessing method was reported as 45% [16], and that of the new method was predicted as 65% in our preliminary study (unpublished data). We set α as 0.05 (bilateral), power as 0.90 and obtained the sample size *N*1 = *N*2 = 128 by PASS 11. To compensate for a loss to follow-up, we set the final sample size as 280 in all.

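### The interim plan puts one look at full enrolment, adds a second unreconciled schedule and ties sample-size change to the observed arm difference, so it neither protects the 5% level nor fixes the final analysis

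*Protocol article*

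**What the plan says.** All of this is in the protocol article.

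- **Data monitoring, first paragraph:** "An interim analysis will be performed when each group has 140 subjects with a completed 12-month follow-up". This look is to revisit the sample-size assumptions. If the share of patients with a PTH ratio of at least 1.5 is clearly higher in the experimental arm (no threshold given), "the sample size will be re-estimated unless the trial has to be stopped as a result of the interim analysis".
- **Data monitoring, second paragraph:** "We will perform an interim analysis of each 70 subjects, which focuses on differences of PA survival with different methods". Graft survival, defined by that ratio, is the primary outcome in the Abstract and under Study design.
- **Sample size calculations:** "We set α as 0.05 (bilateral), power as 0.90 and obtained the sample size", which is 128 per group. Then "To compensate for a loss to follow-up, we set the final sample size as 280 in all", which the Abstract splits as 140 and 140.
- **Study design, bias-reduction measures after Fig. 1:** the "investigator performing the statistical analyses will be blinded to treatment assignments until the final analysis is completed".

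**The concern.** An interim analysis has to come before the planned end of data collection. The first one here does not: it needs every enrolled patient to complete 12 months, although the plan adds patients because it expects losses. The next paragraph gives a different schedule and does not say how the two fit together.

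The re-estimation trigger is the observed difference between arms, with no threshold, cap or matching test. It operates when the result is already favourable, which is when extra patients are least needed. Stopping is also foreseen, while the sample size reserves no alpha for it.

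Two things are at stake. One is the error rate of the primary comparison. The other is whether a reader can tell, before the data are seen, when enrolment ends and which analysis answers the question.

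**Working it through.** **1. Reproduce the plan's figure.** Inputs from Sample size calculations: 45% vs 65%, two-sided alpha 0.05, power 0.90. With a pooled null variance and no continuity correction, and mean rate 0.55:

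n = [1.960·√(2·0.55·0.45) + 1.282·√(0.45·0.55 + 0.65·0.35)]² / 0.20² = (1.379 + 0.883)² / 0.04 = 127.9, so **128 per group**.

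This is the stated figure. It is a fixed-sample calculation that spends the whole 0.05 once. Power is 90.0% at 128 per group and 92.4% at 140.

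**2. Can the first interim be reached?** Implied loss is 1 − 128/140 = 8.6% (24 of 280). At that loss, 140 completers per group would need about 140 × 140/128 = 153 randomised per group, which is more than the trial plans. With no loss at all, the look coincides with the final analysis.

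**3. Number of looks under the second sentence.** If 70 means per group, the looks fall at 70 and 140 per group (two). If it means every 70 in total, they fall at 70, 140, 210 and 280 (four).

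**4. Type I error if each look is a 0.05 test that can stop the trial or claim success (assumption).** The statistics are jointly normal with correlation √(tᵢ/tⱼ) at information fractions t. The error is 1 − P(all |Zᵢ| ≤ 1.96).

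| Looks | Normal theory | Simulated chi-square, null rate 45% |
|---|---|---|
| 140 per group only | 5.0% | 4.8% |
| 70 and 140 per group | 8.3% | 8.1% |
| Every 70 in total | 12.6% | 11.9% |

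**5. Re-estimation (assumption: the sample is doubled, since the plan gives no size).** Here the only earlier test is the one at 140 per group.

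- Claim success if significant at 140 per group; extend only if z lies between 0.5 or 1.0 and 1.96; test again at 280 per group. Type I error is about 6.5% (lower limit 0.5) or 6.2% (lower limit 1.0).
- Extend whenever z exceeds a trigger between 0.5 and 1.96, and test once at the end. Type I error is about 3% to 5% and does not exceed 5%.

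**6. What a bounded design would need.** With one interim and an O'Brien-Fleming-type spending function (0.025 per side), the two-sided alpha spent at fraction t is 4·[1 − Φ(2.241/√t)].

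- t = 70/140: interim about 0.003, final about 0.049, power at 128 per group about 89.9%.
- t = 70/128: interim about 0.005, final about 0.048, power about 89.7%.

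**The case against.** The strongest reply is that stopping boundaries are commonly left to the statistical analysis plan, which is not shown, and that a journal article condenses the full protocol. That stands: the absence of a boundary is not itself the defect, and a reader should not infer that the trial's error rate is in fact 8% to 13%. The stopping clause sits in the paragraph about 140 per group. The sentence about 70 subjects gives no test level, stopping rule or claim.

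It is also tempting to say that extending on a favourable trend inflates the error by itself. It does not. Inflation needs the added rule of claiming success if significant and extending if not, which the protocol does not state. A trend of z between 0.5 and 1.96 at 140 per group is a difference of about 3 to 12 points against a planned 20, so it hardly fits a trigger worded as a clear advantage.

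If 70 means per group, the two paragraphs could form one sequence with its last look mislabelled. Nor do the documents show that blinding is broken. An independent Data Monitoring Committee is named, and arms can be compared under coded labels.

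What remains is what the text fixes itself: an interim at full enrolment, a second schedule with two readings, and a trigger based on the arm difference without a threshold. An analysis plan cannot repair these while the protocol says otherwise.

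**Conclusion.** The Data monitoring section is unworkable as written and needs correcting. It does not protect the two-sided 5% level, and it does not fix which analysis is the trial's answer. The stronger statement, that the 5% level is breached, is not supported, because the protocol does not say what is tested or decided at each look.

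The size is conditional. Type I error is about 8.3% or 12.6% if every look is an unadjusted 0.05 test that can stop the trial or claim success. It is about 6.2% to 6.5% if only the full-sample test is used and the trial is doubled after a positive but non-significant result. There is no inflation if extension is followed by a single final test. The unreachable 140-per-group interim depends on none of these assumptions; it follows from the plan's own 128, 140 and 280. The interim comparison by arm and the analyst blinding are a point to reconcile, not a proven conflict.

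**What to change.** Replace both Data monitoring paragraphs with one schedule and delete the interim at 140 per group. Then choose one of two options:

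1. **Non-inferential looks.** State that interim looks cannot lead to stopping for efficacy or to a claim, and that the primary comparison is tested once, at the end. This costs no alpha.
2. **One bounded interim.** Hold it when about 70 per group have the 12-month ratio, and have someone other than the blinded analyst report it to the Data Monitoring Committee. Use an O'Brien-Fleming-type spending boundary computed at the actual information fraction (about 0.003 then 0.049 at 70/140, or about 0.005 then 0.048 at 70/128). Power at 128 per group falls from 90.0% to between 89.7% and 89.9%.

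Timing favours the first option. Trial status gives April 2016 to December 2018, about 32 months. If that span includes the 12-month follow-up, enrolment lasts about 20 months. With even accrual, 70 per group would reach 12 months at about month 22, too late to spare any enrolment.

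If re-estimation is kept, base it on the pooled blinded proportion with a ratio of at least 1.5, not on the arm difference, and state a maximum size. Say who sees data by arm, so that the interim agrees with the blinding statement under Study design. Record any look already taken and what was decided. Otherwise the cost is protocol wording.
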